**Protocol Authorisation:**

**Chief Investigator**: **[name]: _________**

**Sponsor Representative [name] ___________________________ Date: _________**

**Trial Director-[name] ________________________________ Date: _________**

**Independent Chair-[name]: _________**

**Trial Synopsis**

| **Name of Sponsor** | East Kent Hospitals University NHS FoundationTrust |
| --- | --- |
| **Title of the Study** | A randomised, double-blind placebo-controlled trial of Memantine in the treatment of the Agitation in Alzheimer’s Dementia |
| **Trial Acronym** | MAGD – Memantine for AGitation in Dementia |
| **Investigators** | [name] (Principal Investigator); [name], [name] , [name], [name], [name], [name], [name], [name] |
| **Study Centre(s)** | Kent and Medway NHS and Social Care Partnership Trust, Oxleas NHS Foundation trust; Peterborough, Berkshire NHS Mental HealthFoundation trust, Oxford and Buckinghamshire NHS foundation trust; Plymouth |
| **Study Period** | September 2007 to May 2010 |
| **Objectives** | **Primary Objectives:** To determine the efficacy of Memantine in the treatment of acute agitation in Alzheimer’s Dementia.  **Secondary Objectives:** To estimate the overall symptom response rate to Memantine in the trial population. To investigate whether there are any adverse effects of Memantine in this population. |
| **Methodology** | A 6 week placebo controlled RCT of Memantine in AD with a blind extension to 12 weeks . Planned enrolment is 164. Patients and their clinician’s may withdraw from the study because of a clinically significant worsening in their psychiatric symptoms. These cases and those remaining under double-blind conditions will be followed for a total of 12 weeks. This will enable us to i)maximise the safety data on Memantine and ii)facilitate recruitment into the study, while retaining a strict 12 week RCT. |
| **Number of participants** | 164 |

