About 65% of patients with severe Alzheimer's Disease (AD) will have symptoms of agitation (Hope et al 1999). There are drawbacks associated with the currently available therapeutic interventions for agitation associated with Alzheimer's Disease. In a recent trial, in the group of patients with moderate to severe AD treated with memantine, there were fewer incidences of agitation (Doody et al 2005). There is therefore a clear need for shorter scale pragmatic trial in this area to consider the anti-agitation effect of memantine in the acute progressive phase in AD. It is hypothesized that memantine will be effective in reducing the symptoms of agitation associated with moderate to severe Alzheimer's Disease.

- 1. **Risks & Benefits**

Memantine has a favourable safety profile (Alva et al 2005; Doody et al 2005, Livingston and Katona 2005; Reisberg et al 2003). The current medication provision for agitation has a very limited evidence base and is not without morbidity issues for example over-sedation with some antidepressants and falls with antipsychotics. Memantine is a potential treatment with low morbidity even in comparison to the cholinesterase inhibitors. It may offer practical advantages over other drugs but there have been no RCTs which have looked at under 12 weeks.

1. **Objectives & Purpose**
   1. **Primary Objective**

To determine the efficacy of Memantine in the short term treatment of Agitation in Alzheimer’s dementia.

- 1. **Secondary Objectives**

1. To investigate the effect of Memantine on the subtypes of agitation such as verbal and physical aggression plus other sub-groups.
2. To investigate the effect of Memantine on other secondary outcome measures, namely activities of daily living, other BPSD symptoms specifically mood and psychosis, the need for rescue pharmacological intervention such hypnotics and antipsychotics, cognitive functioning**.**
3. To investigate what baseline factors predict clinical response.
4. To investigate whether there are any adverse effects of Memantine treatment in the study population.

5. To investigate the effect of Memantine on quality of life measures.

1. **Trial Design**
   1. **Description of Overall Trial Design and Plan**

A double-blind, randomised placebo controlled trial of Memantine for agitation in Alzheimer’s disease

164 Eligible Consenting subjects with AD and Agitation

Study Group

Randomisation

Baseline assessment

Placebo Group

2 week assessment

6 week assessment

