During the study patients will be allowed to continue taking stable doses of concomitant medicines including antidepressants, antihypertensives, anti-inflammatory drugs, atypical anti-psychotics, anticoagulants, laxatives, diuretics, hypnotics and benzodiazepines (Tariot et al, 2004). Concomitant administration of anti-parkinsonian medication will be permitted but stable dose and no patients on amantadine this is to avoid difficulties with PD stability as Memantine can have benefit in PD. Cholinesterase inhibitors will not be permitted unless patients have been stable on that medication for at least 3 months. The commencement of new psychotropic medications will not be permitted during the study except for rescue treatment as per guidelines (appendix 6) for managing the behavioural symptoms of dementia.

- - 1. **Consent / Assent**

The patient or patient’s legally authorized representative must provides written informed consent (with the patients assent) to participate in the trial

- - 1. **Subject Identification**

Patients assessed for eligibility (*prior to consent / assent for participation in the trial*) will be assigned an **identification number.**

Once randomised into the trial (*post consent / assent for participation into the trial*) a subject will be assigned a **randomisation code.**

- - 1. **Stopping Rules** There are two criteria for removal of subjects from the trial;

1. Unblinding will occur in the event of life-threatening change in physical state or need for urgent medical and/or psychiatric intervention as requested by the patient’s treating physician in consultation with the study team and study monitoring committee.

2. Drop out from the 12 week-phase of the study is permitted due to intolerable side-effects and clinically significant persistent uncontrolled agitation. This will be a primary end point but will not necessitate un-blinding for that patient.

If patients withdraw their consent for follow-up then, if at all possible, the reason for loss to follow-up should be ascertained and permission should be requested to use data collected already for the purposes of the trial. No further data will be collected on patients who withdraw from follow-up. They have the right not to give a reason for withdrawing from follow-up and also to request that no data is held on them.

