Safety and tolerability will be assessed by descriptive statistical methods. Frequency of adverse events will be tabulated by treatment groups. No statistical comparisons will be performed for the safety parameters.

- - 1. **Planned Recruitment Rate**

Recruitment is expected to start on 3d January 2007. Randomisation is expected to start on 3RD January 2007. Recruitment is planned to finish October 2009. We have assumed that the recruitment rate will be linear across the trial period. The actual recruitment and randomisation targets are given below.

| Month | Recruitment Target | Cumulative target |
| --- | --- | --- |
| 10/2007  11/2007  12/2007  01/2008  02/2008  03/2008  04/2008  05/2008  06/2008  07/2008  08/2008  10/2008  11/2008  12/2008  01/2009  02/2009  03/2009  04/2009  05/2009  06/2009  07/2009  08/2009 | 4  4  8  8  8  8  8  8  8  8  8  8  8  8  8  8  8  8  8  8  8  4 | 4  8  16  24  32  40  48  56  64  72  80  88  96  104  112  120  128  136  144  152  160  164 |
| Total | 164 | 164 |

- - 1. **Analysis Plan**

The final analysis plan will be determined in consultation with the statistician. We will summarise the change in CMAI score from baseline to 6 weeks using mean(sd). The main analysis will be a 2-group (memantine vs placebo) comparison for this variable. We will perform analysis on both LOCF and OC data,
 A 2-sample t-test, which is equivalent to a two-way analysis of variance. We will involve standard survival analysis for remaining in trial and between-group ANOVA for clinical measures. Secondary outcomes will be examined.

1. **Data Management**

A data management protocol will be written to cover laptop security and use; anti-virus software; the handling of personal information; data transfer; data collation, cleaning and verification; data back ups; the data query procedure; and data archiving.

- 1. **Access to Source Data / Documents**

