**DATE:**

Please tick the appropriate boxes for any adverse events and rate intensity (1=Mild, 2=Moderate, 3=Severe)( *Relationship to Study Drug rated: 1=No, 2=Unlikely, 3=Unknown, 4=Likely):

Please tick if reported by patient Present Intensity (1-3) Relationship to Drug*

Headache

Fatigue

Somnolence

Confusion

Hallucinations

Constipation

Vomiting

Dizziness

Gait abnormal

Seizures

Please describe any others:

Other 1

Other 2

Other 3

Comments + action taken

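### Adverse effects are a secondary objective, but the protocol bars any statistical comparison of safety, so no between-arm estimate of harm or its uncertainty is planned

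*Protocol*

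**What the plan says.** The Trial Synopsis lists as a secondary objective "To investigate whether there are any adverse effects of Memantine in this population", and the Secondary Objectives in the body repeat it: "To investigate whether there are any adverse effects of Memantine treatment in the study population". The synopsis also justifies following withdrawn and continuing patients to 12 weeks partly on safety grounds: "This will enable us to i)maximise the safety data on Memantine".

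The analysis is fixed at the end of section 6.7.5. "Safety and tolerability will be assessed by descriptive statistical methods"; adverse-event frequencies are to be tabulated by treatment group; and "No statistical comparisons will be performed for the safety parameters". The Safety population (section 6.7.4) is every randomised patient who took at least one dose.

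Two other statements bear on the point. Section 6.7.1 says that interval estimates will accompany hypothesis tests. The Analysis Plan at the end of section 6.7 says: "We will involve standard survival analysis for remaining in trial and between-group ANOVA for clinical measures".

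**The concern.** Whether a drug causes adverse effects is, in a placebo-controlled trial, a question about the difference between arms. The protocol sets that question, collects the data, and then excludes the comparison that would answer it.

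Frequencies side by side can mislead in both directions. Equal counts may be read as showing no adverse effects when the data still allow an excess of several percentage points. A small excess may be read as harm when it is compatible with chance. With 82 patients per arm, both situations are likely for individual events, and a table of counts does not tell the reader how wide the uncertainty is.

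**Working it through.** **Does anything else in the protocol supply the missing estimate?**

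- *Section 6.7.1, interval estimates.* The sentence attaches intervals to hypothesis tests. No safety test is planned, so it does not clearly reach safety. There is no contradiction between the two sections.
- *Survival analysis for remaining in trial.* Under Stopping Rules (6.2.5), "Drop out from the 12 week-phase of the study is permitted due to intolerable side-effects and clinically significant persistent uncontrolled agitation". Leaving the trial therefore mixes intolerance with lack of effect, and the analysis cannot isolate harm.
- *Responder endpoint, section 6.7.5.* This binary outcome does get an odds ratio with a 95% interval. Harm gets nothing comparable.

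**How much uncertainty would bare counts hide?**

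The protocol states no safety figure to reproduce. The inputs are:

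- 82 patients per arm (section 6.7.2: 164 in total, allocated 1:1), assuming that every randomised patient takes at least one dose;
- event counts, which are assumed, because the protocol gives no adverse-event rates.

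Method: Newcombe score interval for a risk difference d = p1 - p2. With Wilson 95% limits (l1, u1) and (l2, u2) for the two arms,

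- lower = d - sqrt[(p1 - l1)² + (u2 - p2)²]
- upper = d + sqrt[(u1 - p1)² + (p2 - l2)²]

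Worked case, 8 of 82 on memantine against 4 of 82 on placebo, in percentage points:

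- p1 = 9.76, Wilson limits 5.03 to 18.09; p2 = 4.88, Wilson limits 1.91 to 11.88; d = 4.88
- lower = 4.88 - sqrt(4.73² + 7.00²) = 4.88 - 8.45 = -3.6
- upper = 4.88 + sqrt(8.33² + 2.97²) = 4.88 + 8.84 = 13.7

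| Events, memantine v placebo | Risk difference (points) | 95% CI (points) |
|---|---|---|
| 0 v 0 | 0 | -4.5 to 4.5 |
| 4 v 4 | 0 | -7.6 to 7.6 |
| 8 v 4 | 4.9 | -3.6 to 13.7 |
| 12 v 4 | 9.8 | 0.5 to 19.4 |

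A doubling from 4 to 8 patients is compatible with no effect, while a tie at 4 each is compatible with an excess of more than 7 points.

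**Would significance tests be the better remedy?**

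No. At 82 per arm and two-sided 5%, 80% power needs true rates of about 5% v 19.5%, 10% v 27% or 20% v 40%. Estimates with intervals suit this trial; tests do not.

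**What does adding intervals cost in chance findings?**

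The Adverse Event Recording Form in Appendix 4 lists 10 terms. Serious events and deaths make about 12 intervals. Taking them as independent, with no true effect:

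- Nominal chance that at least one excludes zero: 1 - 0.95¹² = 0.46.
- Exact chance for this method at 82 per arm, summing both binomial distributions over all count pairs whose interval excludes zero:

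| True rate of every event | Chance per interval | At least one of 12 |
|---|---|---|
| 2% | 0.0102 | 1 - (1 - 0.0102)¹² = 12% |
| 5% | 0.0358 | 1 - (1 - 0.0358)¹² = 35% |
| 10% | 0.0492 | 1 - (1 - 0.0492)¹² = 45% |

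**The case against.** The best defence is that descriptive safety reporting without p-values is common and reasonable in a trial this small. The objective speaks of investigating adverse effects and names no harm hypothesis or margin. Frequencies by arm on an appropriate population do address it, and the layout of safety tables usually belongs to the SAP, which is not shown. The excluded comparisons could also be read as significance tests only, in which case intervals would already be allowed. Finally, a dozen unadjusted intervals can themselves produce spurious signals.

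Much of this stands. Avoiding tests is right, and the fix keeps that. The chance of a spurious signal is real, as the figures above show, and a descriptive label reduces the risk of misreading without removing it. The illustrative widths would apply to any trial of this size.

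Two parts do not carry. The protocol is not silent and leaving detail to the SAP: it states an exclusion, which a compliant SAP would carry forward. And if the exclusion was meant to cover tests only, saying so costs nothing and the proposed wording should be uncontroversial.

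**Conclusion.** The concern holds, as a modest reporting weakness. The protocol asks a between-arm question about harm and, on the natural reading of section 6.7.5, plans no between-arm answer and no statement of precision. Nothing is biased and no efficacy result changes.

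A reader could recover the intervals from the published table, provided it counts patients. Section 6.7.5 promises only frequencies of adverse events and does not say whether patients or events are counted.

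For illustration, at 82 per arm the data would leave open an excess of about 4.5 points with no events in either arm, and of about 7.6 points with 4 in each. These figures rest on assumed counts and on all randomised patients entering the Safety population. The change is worth making because it is cheap and lets the trial answer its own secondary objective.

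**What to change.** Replace the exclusion in section 6.7.5 with:

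> No significance tests will be performed for safety parameters. For each adverse-event term on the recording form, serious adverse events and deaths, the number and percentage of patients by arm and the between-arm risk difference with 95% CI (Newcombe score method) will be reported over the Safety population, labelled descriptive and without multiplicity adjustment.

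Add stopping for side-effects only where the reason for stopping is recorded. The non-serious form has no dedicated field for it, and action on study drug is structured only on the serious-event form. Leave to the SAP how events already present at week 0 are counted, since the adverse-event form is also completed at baseline.

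The cost is one sentence and one table column. No extra patients are needed. The ten form terms are collected at every visit under the Appendix 1 schedule, and serious events and deaths have their own form, so no new data are needed either. The price is the chance, set out above, that some unadjusted intervals exclude zero with no true effect.

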| Medication dispensed | X | X | X | X | X |
| Subject summary | X | X | X | X | X |

**Eligibility Assessment**

Name: DOB: Identification no.

Randomisation code: Date at baseline:

Investigator: Centre:

| **Inclusion checklist** | **Y or N** |
| --- | --- |
| Can consent/assent |  |
| Meets Mckann Criteria + Hachinski</=4 |  |
| CMAI>/= 39 |  |
| Agitation considered problematic. |  |
| Symptoms present for >2 weeks |  |
| In patient/Nursing home |  |
| MMSE</=19 |  |
| Age>/=45 |  |
|  |  |

| **Exclusion checklist** | **Y or N** |
| --- | --- |
| Memantine usage in prior 4 weeks |  |
| On Cholinesterase inhibitor for less than 3 months and dose not stable |  |
| Antispsychotic, anti-epileptic, antidepressant, benzodiazepine, lithium, or hypnotic dosage alteration in the 2 weeks prior to the start of study |  |
| Antiparkinsonian medication |  |
| Any contraindication to Memantine |  |
| Hypersensitivity to Memantine |  |
| Severe renal impairment |  |
| Epilepsy, history of convulsions or seizure, or epilepsy, or receiving any anti-epileptic treatment. |  |
| Concomitant usage of NMDA antagonists such as amantadine, ketamine or dextromethorphan |  |
| Concomitant use of Warfarin |  |
| Recent myocardial infarction, uncompensated congestive heart failure and uncontrolled hypertension |  |
| Severe, unstable or poorly controlled medical illness |  |
| Any disability that may interfere with the patient completing the study procedure |  |
| Active Malignancy |  |
| Delirium, pain or any medical illness as a clear cause of agitation. |  |
| Any important drug interactions: Prohibited during study and in the 14 days preceding enrollment/inclusion are: Analgesic dextromethorpan, Dopaminergics- amantadine , Warfarin due to theoretical INR prolongation. |  |

**Does the patient meet all of the Inclusion Criteria** *(Delete as appropriate)* **YES / NO**

**Does the patient meet any of the Exclusion Criteria** *(Delete as appropriate)* **YES / NO**

**Is the patient Eligible for the MAGD Trial?** *(Delete as appropriate)* **YES / NO**

**BASIC DETAILS**

| Identification number |  |  | Patient Initials |  |
| --- | --- | --- | --- | --- |

| Patient DOB | / / 19 |  | Patient Gender | Female / Male |
| --- | --- | --- | --- | --- |

| **Patient Details** | | | | | | |
| --- | --- | --- | --- | --- | --- | --- |
| Title |  | | | | | |
| Forename |  | | | | | |
| Surname |  | | | | | |
| Address |  | | | | | |
| Ethnicity | White | Mixed | Asian | Black | Chinese | Other |

| **GP Details** | |
| --- | --- |
| Title |  |
| Forename |  |
| Surname |  |
| Address line 1 |  |
| Address line 2 |  |
| Address line 3 |  |
| Town |  |
| County |  |
| Postcode |  |
| Telephone |  |
| Practice/GP code |  |
| PCT code |  |

| **Alzheimer’s Disease Consultant Details** | |
| --- | --- |
| Title |  |
| Forename |  |
| Surname |  |
| Address line 1 |  |
| Address line 2 |  |
| Address line 3 |  |
| Town |  |
| County |  |
| Postcode |  |
| Telephone |  |
| Department |  |
| NHS Trust |  |

| **Relative/Carer Details** | |
| --- | --- |
| Title |  |
| Forename |  |
| Surname |  |
| Address line 1 |  |
| Address line 2 |  |
| Address line 3 |  |
| Town |  |
| County |  |
| Postcode |  |
| Telephone |  |
| Relationship to resident | Spouse / Sibling / Child / Friend / Neighbour / Parent |
| Gender | Female / Male |

| Basic Details Notes |
| --- |

**Appendix 2-Diagnostic and Staging**

| **ALZHEIMER´S DISEASE:**  **Probable Alzheimer´s disease according to NINCDS-ADRDA criteria (McKhann et al., 1984) –** (Notes to guide application of diagnostic criteria are provided in appendix X)    I. Criteria for the clinical diagnosis of PROBABLE Alzheimer`s disease   -          dementia established by clinical examination and documented by the Mini-Mental Test; Blessed Dementia Scale, or some similar examination, and confirmed by neuropsychological tests; -          deficits in two or more areas of cognition; -          progressive worsening of memory and other cognitive functions; -          no disturbance of consciousness; -          onset between ages 40 and 90, most often after age 65; -          absence of systemic disorders or other brain diseases that in and of themselves could account for the progressive deficits in memory and cognition    v. Clinical diagnosis of possible Alzheimer’s disease:             may be made on the basis of a dementia syndrome, in the absence of other neurologic, psychiatric or systemic disorders sufficient to cause dementia,and in the presence of variations in the onset, in the presentation, or in the clinical course;              may be made in the presence of a second systemic or brain disorder sufficient to produce dementia, which is not considered to be *the* cause of the dementia              should be used in research studies when a single gradually progressive severe cognitive deficit is identified in the absence of another identifiable cause  Meets criteria for Probable Alzheimer’s Disease  Meets criteria for possible Alzheimer’s Disease |                   yes/no  yes/no |
| --- | --- |

**ALZHEIMER´S DISEASE: NOTES/GUIDANCE**

**Probable Alzheimer´s disease according to NINCDS-ADRDA criteria (McKhann et al., 1984)**

I. Criteria for the clinical diagnosis of PROBABLE Alzheimer`s disease

-          dementia established by clinical examination and documented by the Mini-Mental Test; Blessed Dementia Scale, or some similar examination, and confirmed by neuropsychological tests;

The key principles are

1. that the severity of cognitive impairments is sufficient to interfere with social, occupational or practical everyday functioning
2. That a significant degree of cognitive impairment is confirmed using a standardized cognitive test. This could be based on the completed as part of this study, or on a previous assessment using any cognitive assessment instrument with established cut-off thresholds.

-          deficits in two or more areas of cognition;

These can be determined from the study assessment, from a previous recent neuropsychological evaluation or if relevant (eg for praxis) can be inferred from problems with everyday functions. If it is unclear from the study assessment, a more detailed neuropsychological evaluation can be completed if necessary. Areas where deficits are common include memory, attention (eg counting backwards), praxis (eg copying, drawing, completing practical tasks), comprehension (eg following instructions, expression (eg naming objects), verbal fluency (eg listing words, animals), executive function (such as planning, how to deal with problems), abstract thinking (eg similarities and differences, proverbs) and calculation (eg working out change).

-          progressive worsening of memory and other cognitive functions;

There should be some evidence from documented serial cognitive or functional assessments, or from a clinical history that the level of cognitive functioning has declined. This could be inferred by a decline in ability to complete everyday activities, if this is not exclusively related to a physical disability. If someone has been in a nursing home, but only for a short period of time, it will be important to try and find an alternative source of information. Useful sources may be family members or General Practice records. The main goal of this criteria is to exclude “static cognitive impairment” such as may result from a single stroke or head injury.

-          no disturbance of consciousness;

Disturbances of consciousness are seen in people with Alzheimer’s disease, particularly if they experience concurrent delirium which is very common place in the context of minor infections. The goal of this item is to exclude people with a primary diagnosis of delirium. If an individual has ongoing episodes of disturbed consciousness in the absence of a clear, established medical cause; they should not be diagnosed as meeting criteria for probable Alzheimer’s disease but could still meet criteria for possible Alzheimer’s disease.

-          onset between ages 40 and 90, most often after age 65;
-          absence of systemic disorders or other brain diseases that in and of themselves could account for the progressive deficits in memory and cognition

This would include brain diseases such as strokes, Parkinson’s disease, other neurological diseases; and systemic problems such as untreated or severe B12 deficiency or hypothyroidism. Many of these would not however preclude a diagnosis of possible Alzheimer’s disease (see below).

 v. Clinical diagnosis of possible Alzheimer’s disease:

           may be made on the basis of a dementia syndrome, in the absence of other neurologic, psychiatric or systemic disorders sufficient to cause dementia,and in the presence of variations in the onset, in the presentation, or in the clinical course;

            may be made in the presence of a second systemic or brain disorder sufficient to produce dementia, which is not considered to be *the* cause of the dementia

Systemic diseases such as B12 deficiency or hypothyroidism are rarely the direct cause of dementia, and are compatible with a diagnosis of possible Alzheimer’s disease.

Parkinson’s disease, another progressive neurological disease which is an established cause of dementia, or another type of dementia would preclude a diagnosis of possible Alzheimer’s disease. However, evidence of concurrent cerebrovascular disease is entirely consistent with a diagnosis of possible Alzheimer’s disease, unless a patient meets diagnostic criteria for probable vascular dementia (the NINDS AIREN criteria can be used as a guide, requiring clear neurological and neuroimaging evidence of significant cerebrovascular disease and a clear link between the onset of the condition and progression of the impairments and the onset/progression of cerebrovascular events).

            should be used in research studies when a single gradually progressive severe cognitive deficit is identified in the absence of another identifiable cause

